## Abstract

**Objectives:**

The AMANHI study aims to seek for biomarkers as predictors of important pregnancy–related outcomes, and establish a biobank in developing countries for future research as new methods and technologies become available.

**Methods:**

AMANHI is using harmonised protocols to enrol 3000 women in early pregnancies (8–19 weeks of gestation) for population–based follow–up in pregnancy up to 42 days postpartum in Bangladesh, Pakistan and Tanzania, with collection taking place between August 2014 and June 2016. Urine pregnancy tests will be used to confirm reported or suspected pregnancies for screening ultrasound by trained sonographers to accurately date the pregnancy. Trained study field workers will collect very detailed phenotypic and epidemiological data from the pregnant woman and her family at scheduled home visits during pregnancy (enrolment, 24–28 weeks, 32–36 weeks & 38+ weeks) and postpartum (days 0–6 or 42–60). Trained phlebotomists will collect maternal and umbilical blood samples, centrifuge and obtain aliquots of serum, plasma and the buffy coat for storage. They will also measure HbA1C and collect a dried spot sample of whole blood. Maternal urine samples will also be collected and stored, alongside placenta, umbilical cord tissue and membrane samples, which will both be frozen and prepared for histology examination. Maternal and newborn stool (for microbiota) as well as paternal and newborn saliva samples (for DNA extraction) will also be collected. All samples will be stored at –80°C in the biobank in each of the three sites. These samples will be linked to numerous epidemiological and phenotypic data with unique study identification numbers.

**Importance of the study:**

AMANHI biobank proves that biobanking is feasible to implement in LMICs, but recognises that biobank creation is only the first step in addressing current global challenges.

Sub–Saharan Africa and south Asia are the sub–regions with the highest proportion of the global burden of over 289 000 maternal deaths, 6 million child deaths and 2.6 million stillbirth [1–3]. To improve survival and secure attainment of developmental potential of both mothers and their babies, holistic approaches that have future applicability are warranted. A better understanding of the biological mechanisms underlying adverse birth outcomes (such as eclampsia, intrauterine growth restriction, preterm births and stillbirths) and their relationships with various phenotypic, epidemiologic and more importantly epigenetic characteristics will provide a gateway to addressing these challenges.

Evidence from high–income settings suggests that biobanks, which are repositories of biological samples with data linked to individual subjects’ characteristics, may provide a sustained platform with infrastructure for research and discovery of biological mechanisms underlying those leading causes of deaths [4–6]. These mechanisms may have roots in endogenous and exogenous factors (eg, genetic composition, nutrition, environment, etc.) [7–9]. Biological molecules comprising glycomes, proteomes, lipidomes, and other metabolomes that circulate in the blood, other human tissues and body fluids have been linked with detection of risks of adverse maternal and fetal outcomes. For instance, soluble fms–like tyrosine kinase (sFlt–1 or sVEGFR–1) have been found to blunt the beneficial effects of proangiogenic factors on maternal endothelium with consequences such as proteinuria and hypertension (pre–eclampsia) [10–12]. Other biomarkers such as soluble endoglin (s–Eng), P–selectin, Cell free fetal DNA (cfDNA), placental protein 13 (PP–13) are being evaluated as predictors of pre–eclampsia and intrauterine growth restriction (IUGR) [13–18].

However, these factors may vary between developed and developing country populations. If these hypothesized biomarkers prove to be important predictors for these adverse outcomes in developing country settings too, they could potentially allow early risk assessment of pregnant woman in order to promote timely referral and optimal management. The current distribution of bio–repositories is skewed to high income countries (HICs) and their focus of research on ageing and chronic diseases, arguably, may have very limited immediate value for low– and middle–income countries (LMICs) [19,20]. Translating knowledge acquired from developed country settings to implement interventions in developing country settings without testing could be a risky investment. Biobanks are largely lacking in sub–Saharan Africa and South Asia.

Prior to recent initiatives such as the Human Heredity and Health in Africa (H3Africa) by the National Institute of Health, USA [21,22], only few African countries had biobanks [23,24] and almost none in south Asia. In developing country biobanks, biological samples are collected at clinics for focused research into specific infectious diseases and, coupled with weak health systems and poor access to health care, data are rarely systematically collected to make them useful in describing population dynamics, disease and death. Large–scale, population–level epidemiological research with capability to acquire biological specimen that can be linked to morbidity and present and future mortality are crucial if the advantages provided by newly–available high throughput analytical technologies are to be exploited to maximise the public health and clinical relevance of research activities [20].

There are suggestions that developing countries do not have the capacity (the legislation, human resource and logistics such as reliable power supply) to establish and maintain biobanks [25]. Whilst this may be true for now, context also plays an important role in diseases and deaths and so capacity building in these settings is paramount. Fortunately, with the ever–increasing availability of and great advances in high throughput technologies at progressively decreasing cost [20], such biological specimen assays to identify biological markers that predict or are associated with pregnancy–related outcomes, growth and development will have direct global relevance especially for LMICs.

The Alliance for Maternal and Newborn Health Improvement (AMANHI) [26,27] initiative aims to establish the best–characterized cohort of pregnant women and their babies in sub–Saharan Africa and south Asia. This study will contribute to advancing knowledge on key pregnancy and birth outcomes on a sustained research platform, prove the principle that such initiatives are feasible to implement in LMICs and develop local capacity around biobanking and the use to explore future hypotheses.

## Methods

### Study design

This is a population–based, prospective cohort study to collect detailed epidemiological and biological data.

#### Objectives

To uncover biological markers as predictors of important maternal and foetal outcomes. To do this AMANHI biorepository study will:Conduct case–control studies to identify biomarkers that can predict (pre–) eclampsia, preterm births, IUGR, and stillbirths.Replicate the role of genetic variants which have been identified in high–income settings as important determinants of these outcomes through genome–wide association and candidate gene approaches e.g. PSG11, INHBB, ACVR2A, etc. (pre–eclampsia) [11,17,18] and ADCY5, CDKAL1, HHEX–IDE, GCK, etc. (preterm births/low birthweight) [13,28,29].Evaluate the validity of the most commonly proposed existing biochemical, nutritional and inflammatory biomarkers (in serum, plasma or urine), which have been identified from hospital–based studies in high income countries (such as PAPP–A, AFP and inhibin–A (INH), homocysteine, sFlt–1, etc.) [14,30]To facilitate future discoveries in maternal, foetal and neonatal health as new and more feasible methods become available, by establishing a bank/repository of biological samples which collects, stores and maintains samples in a harmonized way across sites in developing countries.

### Overview of the AMANHI Biobanking Study protocol

An on–going surveillance system with longitudinal follow–up of a dynamic cohort of women of reproductive age has been established in all sites–Bangladesh (Sylhet), Pakistan (Karachi) and Tanzania (Pemba Island)–in South Asia and sub–Saharan Africa. These sites were selected because they represent predominantly rural populations within geographic regions of the world with the highest maternal and foetal mortality burden and centres have proven excellent track–record of accomplishment of international research, good leadership and on–going trials will not interfere with the AMANHI biobanking study protocols. All resident women with early pregnancies (before 20 gestational weeks), who intend to stay in the study areas for the entire duration of follow–up, are consented for collection of epidemiological data as well as biological samples for the study. The overall sampling frame is 3000 trios (1000 per site), and the collection process is expected to be functional from August 2014 to June 2016. Unpublished results from the parent studies show less than 5% attrition rates in the population. Many study procedures are similar across sites but the following are site–specific settings for the study:

In Bangladesh this study is being implemented within the Bangladesh Maternal Infection and Preterm Birth (MIST) study by the Project for Advancing the Health of Newborns and Mothers (PROJAHNMO) and the John Hopkins University. All pregnant women are identified through monthly pregnancy surveillance by community health workers (CHWs) and village health workers (VHWs). All pregnancies are confirmed via a strip–based pregnancy tests (Diaspot, marketed by BRESTA) administered by CHW. CHWs, supported by senior staff and study physicians (where needed) consent and enrol pregnant women for the study. All enrolled mothers are placed under e–surveillance using cell phone. Contact numbers are exchanged between women and respective CHWs for ease of communication. The study area is served by six health facilities operated by the Bangladesh Ministry of Health and Family Welfare (MOHFW). Four of them are first level health facilities staffed by a physician or paramedic; these facilities provide a range of preventive care services including antenatal care and normal delivery care. The remaining two are 31 bed hospitals with doctors, nurses, in–patient care and basic laboratory facilities.

In Pakistan, the Biobanking study will be conducted in two peri– urban communities of Karachi, Ibrahim Hyderi (IH) Goth and Bilal Colony Rehri (RG) Goth within the pregnancy and newborn surveillance as part of the Aetiology of Newborn Infections Study in Asia (ANISA) study. Trained CHWs conduct 3–monthly surveillance to identify pregnancies and conduct confirmatory urine dipstick test. Women with confirmed pregnancies are recruited for an ultrasound scan in a study facility whereupon they are enrolled if found eligible. CHWs will be supported by research assistants and study investigators will follow–up on all enrolled women to recruit them to the study centres for sample collection. Phenotypic and epidemiological data will be collected at the homes of the participants. The study area is served by several health facilities–primary to tertiary–but sample collection will be done at IH health centre and the Aga Khan University Hospital.

In Tanzania, the study is being carried out in two of the four districts or “Shehias” of Pemba, the smaller of the two islands of the Zanzibar archipelago. It is a collaboration between the from Johns Hopkins University and local Investigators from Pemba Health Laboratory–IDC and Ministry of Health, Zanzibar. There is an ongoing delivery and neonatal surveillance at facilities and within communities throughout the island as part of the ongoing chlorhexidine (CHx) application to the umbilical cord trial. Consequently, close contacts and communication has been established between the study team, all the Maternal and Child Health (MCH) staff, TBAs and all facilities where deliveries occur on the island. There is a 2–monthly surveillance for identifying pregnancies by CHWs. CHWs provide menstrual calendars to women to record menstrual periods. If the period is missed at two consecutive months, pregnancy tests are performed by local MCH staff or TBA together with a study supervisor. Women are consented for screening ultrasound at study centres and enrolled if found to be eligible. An elaborate system of tracking of pregnant women with the aid of geographical information systems and exchange of mobile contact numbers between participants’ families and study staff. Immediate information about all deliveries is communicated to a central study call centre and the informant is directly linked to the appropriate study team member and designated MCH staff is arranged. This call also helps to get all information regarding stillbirths and location/directions to the household for home deliveries. Mobile clinics are used for following up enrolled women. Two main facilities in the district are being used for biological sample collection.

**Figure 1** shows an algorithm of the strategy for implementing the AMANHI study. The key components of the study protocol are pregnancy and birth surveillance, ultrasound scan to date pregnancy and to enrol women, epidemiological and phenotypic data collection, and biological sample collection, processing and storage.

**Figure 1 F1:**
[figure not shown]
Overview of the study protocol for surveillance and bio–specimen collection within the AMANHI bio–repository study.

*Pregnancy and birth surveillance*: Site specific protocols are as described above. Essentially, in all the three AMANHI sites, all households have been provided unique identification (ID) numbers and have had their geographical coordinates collected and linked to a database. Trained fieldworkers (FWs), predominantly women, perform home visits every 2–3 months to all women of reproductive age in the study area to enquire about pregnancy. If a woman reports or suspects a pregnancy, FWs ascertain the gestational age using the date of her last menstrual bleeding and conduct a urine pregnancy test to confirm. Pregnant women who provide consent undergo a screening ultrasound to date the pregnancy more precisely.

*Consenting*: Fieldworkers consent pregnant women, in their local or preferred languages, to undergo a screening ultrasound scan to date pregnancies accurately. They enroll women if the ultrasound–estimated gestational age of the pregnancy is within the eligibility cut–offs of 8 to 19 weeks. Women are consented for the screening scan, follow–up and biosample collection. However, at each sample collection contact, women are required to provide consent for their babies and their own sample taking. Women’s husbands (fathers of the babies) also consent for their saliva sample collection.

*Early pregnancy dating ultrasound (gold standard for gestational age) and enrolment*: This is the entry point into the study. Recruited women undergo this dating scan at designated AMANHI facilities to determine foetal viability and measure foetal biometric parameters for gestational age determination. Women whose pregnancies are found to be between 8 and 19 weeks of gestation are considered eligible for enrolment. Harmonized protocols have been developed by a consultant in obstetrics and gynaecology and all study sonographers (medically–trained professionals with additional specialist training in ultrasonography) were trained in strategies to improve image quality and to obtain accurate measurements of the biometric parameters. Crown–rump length (CRL) is the biometric measure of choice for foetuses less than 14 weeks whereas bi–parietal diameter (BPD) and femur length (FL) are taken for foetuses at 14 weeks of gestation or more. Quality assurance measures include expert review of images internally (within site) for a random 10% of study subjects and externally (centrally by the consultant in obstetrics and gynaecology) for a random 5% of subjects. Each image is scored based on a quality checklist and sonographers are provided routine feedback for quality improvement.

*Late Pregnancy Ultrasound:* On a subset of mothers, we are also conducting late pregnancy biometry and testing the accuracy of transcerebellar diameter measurements in late pregnancy for gestational age assessment, as compared with early ultrasound based assessment. In the late pregnancy scans, the biometric measurements include bi–parietal diameter (BPD), head circumference (HC), femoral length (FL), abdominal circumference (AC), and transcerebellar diameter (TCD). For this sub–study, all images are being reviewed with stringent quality control and scoring, and routine feedback provided to sonographers.

### Phenotypic and other epidemiological data collection

Trained study fieldworkers (FWs) conduct four home visits to the enrolled women; at baseline (immediately after enrolment), and at 24–28 weeks, 32–36 weeks and after 37 completed weeks of pregnancy to collect routine study data as detailed in **Table 1**. After delivery, three additional visits are made, within 72 hours, on the fourth to the seventh day after birth and after 42 days [26]. Women or newborns with a morbidity or an abnormal urine test and BP results are referred for appropriate care within health facilities. Core variable tables containing the minimum data that should be collected across all sites have been developed. They ensure uniform data are collected across all sites and specify the type of question, the response options and how the data are presented in the databases (text, numeric or string). These core variables tables were translated into questionnaires for phenotypic and epidemiological data collection across sites.

**Table 1 T1:** Type of epidemiological and phenotypic data being collected during home visits

Modality	Details being collected in AMANHI biorepository study	Time of collection
Background characteristics	Demographic, socio–economic, other characteristics of the woman and her household and an asset inventory to be used in constructing an asset index for classifying women into wealth quintiles	Baseline visit
Medical history	Previous obstetric and gynaecological history, history of birth defects and congenital anomalies among previous babies, stillbirths and IUGRs; previous medical and surgical history including medicinal prescription drugs taken or being taken for chronic diseases and periodontal diseases	Baseline and antenatal (AN) visits
Risk factors and exposures	Cigarette smoking, alcohol ingestion, smoke from biomass cooking fuels, occupational chemical exposures, strenuous physical work and the use of narcotics and other drugs	Baseline visit
Depression screening	Depression screening using the 9–question patient health questionnaire (PHQ–9)	AN and postnatal (PN) visits
Anthropometry	Maternal weight and height, maternal mid–upper arm circumference and abdominal girth	Baseline, AN and PN visits
Reported morbidity	Questions about any illness or complications during pregnancy, childbirth and the postpartum period. Care–seeking, hospitalizations and treatment received for any morbidity	AN and PN visits
Assessment for pre–eclampsia	Measurement of blood pressure using a digital (Microlife®) sphygmomanometer (calibrated for hyperdynamic circulation in pregnancy) and testing urine for proteins (Uristix®)	All visits except delivery visits
Nutritional assessment	Food frequency questionnaire	One AN visit and Post day 42 PN visit

There is a passive surveillance system in health care facilities where trained hospital FWs collect clinical data on any facility attendance by women enrolled in AMANHI. These data cover the reason for attending the facility, the details of the treatment given and the outcomes.

Harmonized protocols have been used across sites for training study supervisors (who are experienced fieldworkers who have had experience working in health facilities and provided additional training for newborn handling and assessment) to conduct neuromuscular, physical and feeding maturity assessment within 72 hours of the birth on all babies born to women enrolled in the AMANHI study. They also take neonatal anthropometric measurements (head, chest and mid–upper arm circumference, foot length and breast bud diameter) on the baby during these visits. Trained study clinicians validate 5%–15% assessments through repeat assessments also within the 72–hour window period after birth.

After 42 days of the birth, fieldworkers visit families to collect epidemiological and phenotypic data and whereupon women exit the study.

In case of a maternal, foetal (stillbirth) or neonatal death, uniform protocols and training have been provided to supervisors in all sites to conduct home visits to conduct verbal autopsy interviews with reliable informants to elicit the circumstances leading to the death and any relevant information that may help identify the medical cause of death. Harmonized methods (based on principles of the International Classification of Diseases) are being used to assign the causes of deaths and complete death certificates for each death on a specially designed software platform [27].

### Biospecimen collection and processing

A sampling scheme with a sequence of time points to obtain maternal blood and urine, maternal stool, umbilical cord blood and tissue, placenta tissue and membranes, newborn stool and saliva samples (where cord blood is not available), and paternal saliva samples are used. Samples are collected at enrolment, at either 24–28 weeks or 32–36 weeks antenatal visit, at delivery and after 42 days of the delivery. Participants are randomised for antenatal maternal blood and urine collection at either 24–28 weeks or 32–36 weeks gestation in a ratio 2:1. **Table 2** shows the samples collected, the timing of collection and the main extraction from these samples in AMANHI.

**Table 2 T2:** Timing of collection, processing and/or main extraction for AMANHI biological samples

Sample type	Timing of collection	Processing & planned use of the sample
Maternal blood	Enrolment, 24–28 weeks or 32–36 weeks, postnatal day 42–60	For DNA extraction, HbA1C analysis, and serum/plasma extraction, aliquoting and storage
Maternal urine	Enrolment, 24–28 weeks or 32–36 weeks, postnatal day 42–60	Uncentrifuged and centrifuged sample, biochemical and pathological analysis
Cord blood sample	At birth	DNA extraction, HbA1C analysis, and serum/plasma extraction, aliquoting and storage
Cord tissue samples	At birth	RNALater, alcohol, flash frozen and formalin sample
Placenta tissue samples	At birth	RNALater, alcohol, flash frozen and formalin sample
Placenta membrane samples	At birth	RNALater, alcohol, flash frozen and formalin sample
Maternal faeces	At birth	Maternal faecal microbiome
Paternal saliva	Antenatal or postnatal	Paternal DNA
Fetal faeces	Postnatal day 42–60	Newborn faecal microbiome

Standardized protocols are being implemented across all sites. Blood samples of the mother and from the umbilical cord are collected into pre–labelled tubes, centrifuged and serum, plasma and buffy coat aliquots obtained. Aliquots of whole blood samples are also used to perform HbA1C assay and spots were also placed in Whatman cards and dried. Maternal urine samples are similarly centrifuged and RNALater is mixed with sediments and aliquots taken for storage.

Placenta samples are harvested and processed within 30 minutes of delivery and photographs of the surfaces taken. Full thickness tissues samples are harvested in four areas, three of which have a thin layer of maternal tissues sliced off the surface. Samples of the membranes and umbilical cord are also taken. Placental tissue samples are stored in RNALater, alcohol, or are flash frozen. A sample is also stored in formalin solution for histology. The placenta is then weighed and a third photograph is taken before safe discarding.

Maternal and newborn stool samples are being also collected to assess microbiota around the time of delivery and when newborn feeding is established, respectively. A single sample of paternal taken either during one of the antenatal or postnatal visits) and two of newborn saliva (are taken at 42–60 days postpartum from babies whose cord blood could not be obtained at the time of birth) are collected using an Oragene DNA collection kit for DNA extraction. All biological samples are stored at –80°C.

**Outcomes.** The main adverse pregnancy outcomes being evaluated in the AMANHI bio–repository study are (pre–) eclampsia, intrauterine growth restriction, preterm birth and stillbirths.

**Sample size considerations.** In this study, 3000 pregnant women will be recruited from the three participating sites (1000 per site) over a period of one year. Sample size and power considerations were based on the 3% prevalence of pre–eclampsia (the rarest outcome) in the population. The 3000 women from the three sites is only sufficient to detect a 1% (absolute) change in the prevalence of pre–eclampsia with 90% power and at 5% significance level if analyses adopt a case–control design with a 1:3 ratio of cases to controls.

**Confidentiality.** All participants are provided with unique study IDs with which they and their families are identified in the study. All data collected from participants are being kept confidential; hard copies of study–related forms are stored in locked cabinets and soft copies are securely stored on dedicated, password–protected servers. These are only accessible to the principal investigators and approved co–investigators. After completion of the study, any sample to be used for analyses will be de–linked from participant’s identity and only alphanumeric identification numbers will be used.

**Safety issues in sample collection and processing**. All the personnel involved in sample collection and processing are well trained by the sites. AMANHI–specific standard operating procedures (SOP) have been developed and all phlebotomists and laboratory scientist involved have been trained in study participant care, sample collection, sample processing, bio–safety in sample handling and safe disposal of instruments and materials (**Online Supplementary Document(Online Supplementary Document)**).

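### The only power statement joins a 1-point change in pre-eclampsia prevalence to a 1:3 case-control design, and the stated 90% does not hold under that design

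*Protocol article*

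**What the plan says.** The paragraph on sample size considerations (Methods, under biospecimen collection and processing) plans 3000 women, 1000 per site. It sets the basis: "Sample size and power considerations were based on the 3% prevalence of pre–eclampsia (the rarest outcome) in the population". It then says the 3000 women are "only sufficient to detect a 1% (absolute) change in the prevalence of pre–eclampsia with 90% power and at 5% significance level" and attaches a condition: "if analyses adopt a case–control design with a 1:3 ratio of cases to controls". It does not state the number of cases, the direction of the change, whether the test is one- or two-sided, or an effect size for a marker.

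Three other places bear on this:

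- The Objectives give the purpose of the case-control studies as finding biomarkers that predict pre-eclampsia and the other outcomes.
- The biospecimen section divides the second antenatal draw: "Participants are randomised for antenatal maternal blood and urine collection at either 24–28 weeks or 32–36 weeks gestation in a ratio 2:1".
- The overview cites unpublished parent-study results showing "less than 5% attrition rates in the population".

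**The concern.** The effect and the design in the power sentence do not belong together. In a 1:3 case-control sample one participant in four is a case because the analyst chose it so. What is compared is a marker level or exposure frequency between cases and controls. A change in the outcome's prevalence is a cohort quantity.

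This is the only power statement in the article. Anyone planning or approving a biomarker analysis on these samples would look there for the size of effect the study can detect, and would not find it. The limiting factor, about 90 cases of the rarest outcome, is never stated.

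**Working it through.** **Inputs from the article.** N = 3000; prevalence 3%; change 1 percentage point; power 90%; significance level 5%; ratio 1:3; attrition below 5%; second antenatal draw split 2:1. Sidedness is not given. Two-sided is used below unless stated, with z = 1.96 and 1.2816.

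**1. Trying to reproduce the 90% as a two-group comparison.** The generous reading splits all 3000 women 750:2250 and compares two prevalences. With n1 = 750 and n0 = 2250:

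power = Φ{(|p1 − p0| − 1.96·s0) / s1}, where s0 = √[p̄(1 − p̄)(1/n1 + 1/n0)] and s1 = √[p1(1 − p1)/n1 + p0(1 − p0)/n0].

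For 4% in the smaller group and 3% in the larger: p̄ = 0.0325, s0 = 0.00748, s1 = 0.00801. Power = Φ{(0.01 − 0.01465)/0.00801} = Φ(−0.58) = 28%.

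| Smaller group (750) | Larger group (2250) | Power |
|---|---|---|
| 4% | 3% | 28% |
| 3% | 4% | 22% |
| 2% | 3% | 29% |
| 3% | 2% | 37% |

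One-sided testing raises this to 34% to 48%. Dropping the 1:3 ratio for an equal split, one-sided, 3% against 2%, gives the best two-group result, 54%. For 90% power at 1:3, two-sided, the total would be about 13,300 to 19,200 women. This reading is generous in a further sense: 750 cannot be a number of cases when 3% of 3000 are affected.

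**2. A calculation that does come close.** A one-sample test of cohort prevalence against a fixed 3%:

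N = (1.96 + 1.2816)² × 0.03 × 0.97 / 0.01² = 3058.

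At N = 3000 power is 89.5% with the null variance throughout. With the alternative variance it is 86.2% for a rise to 4% and 93.6% for a fall to 2%. There are no controls and no ratio in this calculation.

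**3. Cases available.** 3000 × 0.03 = 90 cases, hence 270 controls. At 5% attrition, 2850 × 0.03 = 85.5, about 86 cases. The 2:1 split leaves about 60 cases with a 24–28 week draw and 30 with a 32–36 week draw.

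**4. What a 1:3 case-control analysis can detect** with 90% power at two-sided 5%, one marker. For a continuous marker the standardised difference is (1.96 + 1.2816)·√(1/n1 + 1/n0); for 90:270 this is 3.2416 × √(1/90 + 1/270) = 0.39. For a binary marker, the power formula in step 1 is solved for the case frequency. Control frequencies of 30% and 10% are assumptions, since the article gives none.

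| Samples | Cases:controls | SD units | OR at 30% | OR at 10% |
|---|---|---|---|---|
| Not affected by the split | 90:270 | 0.39 | 2.2 | 2.9 |
| Same, 5% attrition | 86:258 | 0.40 | 2.3 | 3.0 |
| 24–28 weeks | 60:180 | 0.48 | 2.7 | 3.6 |
| 32–36 weeks | 30:90 | 0.68 | 4.0 | 5.4 |

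**5. Several markers.** With 90:270, a Bonferroni level of 0.05/100 has z = 3.48, giving (3.48 + 1.2816) × 0.1217 = 0.58 SD. At 5e-8, z = 5.45, giving 0.82 SD.

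**The case against.** The best defence is that 3000 and 90% are not arbitrary. They nearly match a one-sample prevalence calculation, and the 1:3 clause may simply describe how later analyses will be run. That stands as a plausible account of the number, so a reader should not infer that the sample size has no basis. It does not rescue the sentence, which makes the 90% conditional on the case-control design.

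A second defence is that the case-control sets would be nested in an enumerated cohort. If sampling fractions are known, absolute risk by marker group can be recovered by weighting. This is right, and it would be too strong to say that such a study can never address prevalence differences. But a weighted analysis cannot be expected to do better than the full 3000, and no two-group split examined there passed 54%.

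Third, the split draw and attrition are side issues. Only the second antenatal blood and urine draw is divided; the enrolment draw and the samples taken at and after birth are not. Attrition moves 0.39 SD to 0.40 SD. A condensed article may also leave sub-sample power to the full protocol. So neither is an error in itself; they matter only for what a restated figure should cover.

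A reader might also quote power for 3% against 4% with 90 cases and 270 controls. That treats an outcome prevalence as if it were a marker frequency, which the article does not give, so it is not used here.

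**Conclusion.** The power claim is wrong as written. Under a 1:3 split of the whole cohort, power for a 1-point difference from 3% is about 22% to 37%, not 90%, and a true 1:3 case-control sample does not compare outcome prevalence at all. The informative number is about 90 cases (about 86 at 5% attrition), enough for moderate to large differences in a single marker.

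These results rest on normal approximations, two-sided 5% testing, the article's own 3% prevalence, and the assumed control frequencies. They allow for no multiplicity, although the Objectives and analysis plan foresee genome-wide, candidate-gene and omics work, so they flatter the study. The one-sample origin of 3000 remains an inference.

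Two further readings are not supported. The error does not show that the biobank is too small for its purpose: the article also justifies it as a platform for future research. Nor does the text show that null biomarker results will be misread; the sentence is phrased as a limit. That is a risk to guard against, not a documented consequence.

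**What to change.** Delete the link between the 1-point prevalence change and the 1:3 design. If the 1-point figure is kept, present it only as a one-sample calculation for whole-cohort prevalence against 3%, with its sidedness and direction.

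For the case-control analyses, state along these lines: at 3% prevalence, 3000 women give about 90 pre-eclampsia cases (about 86 at 5% attrition). With 270 controls, 90% power and two-sided 5% for a single marker without multiplicity adjustment, the detectable difference is about 0.4 SD, or an odds ratio of about 2.2 to 2.9 for an assumed control exposure of 30% to 10%. For the split antenatal draw it is about 0.48 SD or an odds ratio of 2.7 to 3.6 at 24–28 weeks (60:180), and 0.68 SD or 4.0 to 5.4 at 32–36 weeks (30:90). Add that detectable effects are larger after correction for multiple markers, for example 0.58 SD for 100 markers and 0.82 SD at 5e-8 with 90:270.

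The cost is a less favourable stated figure. Recruitment and sampling do not change.
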